### 3.3 General study outline

The total duration of subject participation will be approximately 3 months. The study consists of a screening period, a treatment period and a follow-up period.

At the screening visit, after a consent discussion with the investigator, the subjects will first sign the ICF and then undergo other eligibility evaluations, including collecting of a nasopharyngeal swab sample for SARS-CoV-2 PCR analysis, unless a positive PCR result is already available. Subjects will be enrolled and randomized once the results of the screening assessments are available and the investigator has confirmed the subject's eligibility. A positive test result in SARS-CoV-2 PCR analysis of a nasopharyngeal swab sample taken and analyzed outside of this study may be used for evaluation of virus positivity, if taken within five days of enrolment. Enrolment of subjects without previous PCR-confirmed SARS-CoV-2 virus shedding must have to await a positive SARS-CoV-2 PCR test result of a nasopharyngeal swab sample collected at the screening visit. The participants will be contacted by telephone as soon as the screening test results are available and told whether or not they are eligible for enrolment.

After enrolment and randomization, subjects will proceed to the treatment period. Home delivery of the medication will be arranged by the study sites, and eligible subjects are to start to use their study medication immediately upon its delivery. During the treatment period, the subjects will receive HCQ or placebo capsules twice daily during 7 days, in addition to standard care for Covid-19 infection. Daily telephone contacts by the study sites are included in the standard care protocol; also, they will be used for collection of patient-reported information. On Day 8, all subjects will be contacted by telephone for an interview on symptoms and possible AEs. Approximately 2 weeks and 4 weeks after start of drug intake, the subjects will visit their study site for assessments.

The follow-up period will start at the 4-week visit and will last until 3 months after start of IMP intake. During the follow-up period, information on health care services that the subjects have received in public health care is collected from the Care Register for Health Care, and information on possible deaths is collected from death certificates archived by Statistics Finland. All subjects will be contacted by telephone 3 months after start of IMP intake for an interview on possible AEs and other health outcomes.

After the follow-up period, with the subject's consent, additional post-study follow-up information will be collected from the Care Register for Health Care and from death certificates until 6 months after start of IMP intake.

The study outline is presented in Table 1 below.

**Table 1. Study outline**

| Protocol activities                                             | Screening period | Treatment period | Follow-up period |
|-----------------------------------------------------------------|------------------|------------------|------------------|
| Informed consent                                                | X                |                  |                  |
| Demography and substance use                                    | X                |                  |                  |
| Physical examination                                            | X                |                  |                  |
| 12-lead ECG                                                     | X                |                  |                  |
| Vital signs                                         | X                | X                |                  |
| Laboratory safety assessments                       | X                | X                |                  |
| SARS-CoV-2 PCR analysis of nasopharyngeal sample    | X                | X                |                  |
| SARS-CoV-2 antibody titres in serum sample                      | X                | X                |                  |
| Other Covid-19-related biomarkers in blood samples  | X                | X                |                  |
| DNA sample                                          | X                |                  |                  |
| Eligibility criteria and decision of entry                      | X    | X    |                  |
| IMP administration                                              |                  | X    |                  |
| Patient-reported health outcomes                                | X                | X    | X                |
| Medical history and current medical conditions                  |                  | X                |                  |
| Adverse events (AEs) and serious adverse events (SAEs)          |                  | X                |                  |
| Prior and concomitant treatments                                |                  | X                |                  |
| Evaluation of information from the registers                    |                  |                  | X                |

Vital signs to be taken at the screening visit include systolic and diastolic blood pressure, heart rate, body temperature, respiratory rate and SpO2. Vital signs to be recorded at the 2-week visit include body temperature and SpO2.

Eligibility criteria will be verified and a decision to enter the subject into the study will be made before treatment allocation and dosing; the screening period is completed with a telephone contact between the investigator and the participant at the time when all relevant screening test results become available.

Includes sampling for HCQ concentration analysis

Optional. The DNA sample for pharmacogenetic (PG) evaluations and HLA haplotyping may be collected at any time during the study.

The first 7 days of the treatment period

Includes body temperature and pulse oximetry results recorded at home by the patient, until the 2-week visit

## 4 STUDY PATIENTS/SUBJECTS

### 4.1 Source population

The subjects participating in this study will be adult males and females with PCR-confirmed Covid-19 infection, fulfilling all of the inclusion criteria and none of the exclusion criteria.

### 4.2 Number of study patients/subjects

Approximately 600 subjects are planned to be included in the study. Actual enrolment numbers will depend on the development of the Covid-19 epidemic in Satakunta and other regions of Finland.

### 4.3 Inclusion criteria

1. Subjects over 40 years of age, or 18-40 years of age with one or both of the following:
  - a. diabetes mellitus (type 1 or type 2)
  - b. BMI > 35 kg/m^2.
2. Subjects capable of providing independent informed consent and signing the informed consent form (the subjects' capacity to consent should be determined in accordance with applicable professional standards and will be based on the investigator's judgment).
3. Subjects with symptoms typical of Covid-19 infection, according to criteria specified in the study protocol, with or without known or suspected exposure to the SARS-CoV-2 virus. The onset of symptoms must be within 5 days of enrolment. Study medication may only be started once a positive SARS-CoV-2 PCR test results of a nasopharyngeal swab sample is available; if the first PCR test result is negative, a second sample may be collected and analyzed.
4. Female subjects of child-bearing potential must agree to employ a reliable method of contraception until three months after start of IMP intake.
5. Subject must agree not to share medication with the others.

### 4.4 Exclusion criteria

1. Subjects with suspected severe or moderately severe pneumonia, presenting with any of the following: respiratory rate > 26 breaths/min; significant respiratory distress; or SpO2 ≤94 % on room air;
2. Subjects requiring treatment in the hospital, according to the treating physician's judgement;
3. Subjects having any contraindication to treatment with HCQ, such as a long QTc interval (>450 ms in men, >470 ms in women), porphyria, epilepsy, severe renal insufficiency;
4. Screening 12-lead ECG results showing evidence of clinically significant disturbances of cardiac rhythm or impulse conduction. Atrial fibrillation, paroxysmal supraventricular tachycardia or supraventricular extrasystoles are not exclusionary;
5. Cardiac insufficiency of NYHA Class 3-4;
6. History of stroke, within 6 months of screening;
7. Subjects with a history of seizures within one year of screening;
8. Subjects with a history of drowning accident;

9. Any psychiatric diagnosis or symptoms (e.g., hallucinations, major depression, delusions, schizophrenia, bipolar disorder) that, in the opinion of the investigator, could interfere with study procedures or assessments or subject safety; prior history of suicidal behaviour or suicide attempt within five years of screening will also exclude the subject;
10. Disorder related to alcohol or drug abuse, as defined in DSM-5-TR, within one year prior to screening;
11. Evidence of current or history of any significant autoimmune disease that, in the opinion of the investigator, could interfere with evaluation of the study results or constitute a health hazard for the subject;
12. Evidence of an immune system that is compromised; including, but not limited to, a diagnosis of HIV; or the subject has been splenectomised or has received an organ transplant (corneal transplants excluded), or is receiving chronic systemic immunosuppressive medication;
13. Evidence of current clinically significant and possibly unstable pulmonary, gastrointestinal, renal, hepatic, endocrine, haematological or cardiovascular system disease or metabolic disturbance;
14. Diagnosis of cancer (haematological or solid tumour) for which the subject is currently being treated, or for which there is evidence of active disease. Subjects with local prostate cancer or local dermatological tumours, such as basal or squamous cell carcinoma, may be included;
15. Any clinically significant abnormalities in laboratory tests, vital signs, ECG or physical examination findings at screening that in the opinion of the investigator require further investigation or treatment or may interfere with study procedures or safety. These may include, but are not limited to, the following:
  - a. estimated glomerular filtration ratio (eGFR)  $< 30 \text{ ml/min/1.73 m}^2$ , based on the CKD-EPI equation;
  - b. a plasma total bilirubin value  $> 2$  times the upper limit of the reference range;
  - c. plasma alanine aminotransferase (ALT) or aspartate aminotransferase (AST) value  $> 3$  times the upper limit of the reference range;
16. Current or anticipated use or recent prior use (pre-study time limits specified in Section 5.4 of the protocol) of disallowed concomitant treatment; use of concomitant medications that prolong the QTc interval is not allowed (see Appendix 1);
17. Having received in another clinical trial any other investigational medication (unless it can be documented that the subject received only placebo) within 3 months or 5 half-lives (whichever is longer) before screening;
18. Disease or medication that, in the opinion of the investigator, could seriously impact the assessments of safety, tolerability or efficacy.
19. Pregnancy or breast-feeding.

#### 4.5 Recruitment

Possibly eligible adults who contact the study sites to seek medical care for possible Covid-19 infection will be recruited for the study.

At first, the study is briefly described to the subject candidate in layman's language, and the main inclusion and exclusion criteria are checked. If an exclusion criterion is fulfilled, this is immediately told to the candidate, and the interview is terminated with possible health-related instructions. If a positive SARS-CoV-2 PCR analysis result of a nasopharyngeal swab sample is already available at this stage, a screening visit is booked if the candidate might be suitable for the study. If a positive PCR test result is not available, the person is instructed to undergo the standard Covid-19 testing procedure employed by the study site, if indicated on clinical grounds. The study ICF will be presented to subject candidates by suitable and

available methods, and a consent discussion will be carried out at the start of the screening visit. Upon the subject candidate's wish, the subject may then sign and date the ICF in the investigator's presence.

The management of patients with suspected Covid-19 infection or Covid-19-related concerns will not otherwise be impacted by whether or not the person in question is willing to consider participation in this study.

#### 4.6 Instructions concerning lifestyle and concomitant treatments

Female subjects of childbearing potential will have to agree to use a reliable method of contraception until three months after start of IMP intake, if they practice heterosexual intercourse. Reliable contraception methods include reliable oral, transdermal or injectable hormonal contraceptives, intrauterine devices, hormonal intrauterine system, barrier methods (e.g. male or female condom) or having a male partner who is sterile (e.g. vasectomised).

Fasting is not required for the blood tests to be taken on the screening visit, 2-week visit or 4-week visit.

For instructions and restrictions regarding concomitant treatments, please see Section 5.4.

#### 4.7 Withdrawal of subjects

A subject has the right to withdraw his/her consent without any need to justify this decision. However, efforts should be made to find out the reason of the withdrawal. Possible withdrawal will not have any negative effect on the subject's future medical care.

The investigator may withdraw a subject from the study at any time based on the investigator's clinical judgement. A subject will be withdrawn from further IMP dosing if he or she starts a prohibited medication, develops suspected severe or moderately severe pneumonia, requires treatment in hospital, or other inclusion and exclusion criteria are no longer met. A subject will also be withdrawn from further IMP administration if she/he fails to comply with the trial protocol, or an AE jeopardizing her/his well-being occurs, or if the discontinuation is otherwise in the best interest of the subject.

Subjects who discontinue the study drug prematurely will be encouraged to attend all study visits and complete all study assessments. Still, subjects will retain the right to withdraw their consent for the study, and no study procedures should be carried out against their will.

All information collected from a withdrawn subject, including the reason of withdrawal, will be included in the study file for use as study data and for purposes of verification.

### 5 TREATMENTS

#### 5.1 Investigational treatment

HCQ capsules (re-formulated from Oxiklorin 100 mg tablets, manufactured by Orion Pharma) will be dispensed to the study participants to allow dosing according to the

following regimen: 300 mg twice daily, to be taken with meals, for one day, and then 200 mg twice daily, to be taken with meals, for 6 days. IMPs will be re-formulated, packed and labeled for dispensing by the hospital pharmacy of Satakunta Central Hospital (SataDiag).

## 5.2 Reference treatment

Placebo capsules (containing cellulose and magnesium stearate) will be dispensed to the study subjects in identical containers as HCQ, to be taken twice daily with meals, for seven days. The placebo capsules will be formulated, packed and labeled for dispensing by the hospital pharmacy of Satakunta Central Hospital (SataDiag).

## 5.3 Handling of the study products

Manufacturing, packaging, and labelling of the IMPs will comply with GMP regulations. The IMPs are to be stored at below 25°C, out of reach of children.

## 5.4 Prior and concomitant treatments

All concomitant treatments administered during the study, including the post-treatment period, must be recorded on the CRF page for concomitant treatments. In order to assess subject eligibility, medications used within 4 weeks prior to the screening visit will be recorded.

No other investigational treatment is allowed to be used during the study.

Use of immunosuppressive drugs, such as methotrexate, oral glucocorticoids and interferon products, is prohibited during the treatment period and four weeks before the start of the study treatment.

Use of concomitant medications that may prolong the QT interval is not allowed during the treatment period and in the two weeks before the start of the study treatment. Medications prohibited because of their possible effects on the QT interval are listed in Appendix 2 of this study protocol; a Finnish-language version of this list is also included as an appendix of the ICF.

## 5.5 Procedures for monitoring of subject compliance

Treatment compliance will be evaluated by asking the participants to register any deviations from the planned treatment regimen in a participant diary to be collected at the 2-week visit and by performing concentration analysis of HCQ in blood samples collected at the 2- and 4-week visits.

# 6 VISIT SCHEDULE

## 6.1 Screening

At the screening visit, the potential study subject will first receive written and verbal information on the study and will have an opportunity to ask questions. If a subject decides to participate in the trial, written informed consent will be obtained before any study-related procedures are performed. A copy of the signed ICF will be provided to the subject.

At screening, subjects will be interviewed for their medical and surgical history, use of medications and current medical conditions, including symptoms of Covid-19 infection and possible exposure to the SARS-CoV-2 virus. The screening interview includes a review of the subject's mental health status, with particular attention to suicidal behaviour and suicide attempts in the past five years. Based on the subject's consent given in the ICF, any existing relevant medical records of the subject will be reviewed and copies thereof will be filed in the subject's source data file. A nasopharyngeal swab sample for SARS-CoV-2 PCR analysis will be taken from those subjects who have not yet undergone such testing for Covid-19 infection; most study participants will already have a positive SARS-CoV-2 PCR analysis result available at this time. Each subject will undergo a physical examination. Blood samples will be collected for screening laboratory tests and for later analysis of SARS-CoV-2 antibodies and other Covid-19-related biomarkers. Demographic data, 12-lead ECG and vital signs will be recorded, and the GAD-7 questionnaire will be completed by the subject. For a more detailed description on the information to be collected at the screening visit, please refer to Section 7.1.

Subjects will be enrolled and randomized once the results of the screening assessments are available and the investigator has confirmed the subject's eligibility. A positive test result in SARS-CoV-2 PCR analysis of a nasopharyngeal swab sample taken and analyzed outside of this study may be used for evaluation of virus positivity, if taken within five days of enrolment. Enrolment of subjects without previous PCR-confirmed SARS-CoV-2 virus shedding must have to await a positive SARS-CoV-2 PCR test result of a nasopharyngeal swab sample collected at the screening visit. If the first PCR test result is negative, a second sample should be collected and analyzed.

As all screening test results will not be available at the screening visit, the participants will be contacted by telephone on the next day (or as soon as the screening test results are available) and told whether or not they are eligible for enrolment. Health-related instructions will be given, and eligible subjects will be told that they should start to use their study medication immediately upon its delivery. Home delivery of the medication will be arranged by the study sites.

## 6.2 Treatment period

The treatment period will last 4 weeks and the actual treatment 7 days. During the treatment period, the subjects will receive HCQ or placebo capsules twice daily with meals during 7 days. In addition, all subjects will receive standard care for their Covid-19 infection, according to local treatment practice. This includes daily telephone contacts with patients who have symptoms. The script of the daily telephone interviews includes questions on possible suicidal ideation and impairment of mental health. Should the answers to these questions reveal significant adverse changes from baseline or an elevated risk for self-harm, the investigator will be informed, and will then take the necessary actions to provide appropriate psychiatric evaluation and care for the subject, without delay. The subjects will be provided with finger-tip pulse oximetry devices and with instructions on their use during the first 14 days of the treatment period.

On Day 8, all subjects will be contacted by telephone for an interview on symptoms, concomitant medications and possible AEs.

Approximately 2 weeks and 4 weeks after start of drug intake, the subjects will visit their study site for assessments. Safety laboratory tests will be taken at these visits, as well as nasopharyngeal swab samples for SARS-CoV-2 PCR analysis and blood samples for analysis of SARS-CoV-2 antibody titres, other Covid-19-related biomarkers and HCQ concentration analysis. The GAD-7 questionnaire will be completed by the subjects. In addition, they will be asked about symptoms, concomitant medications and possible AEs that might have occurred since the last contact. At the 2-week visit, body temperature and SpO2 will also be measured, and the participant diaries will be collected.

Because of the slow elimination of HCQ, the treatment period of this study is defined as starting from the first IMP intake and ending at the 4-week visit.

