### 7.2.2 Patient-reported health outcomes

During the first two weeks of the treatment period, the subjects are asked to report their symptoms (including body temperature and SpO2) in the form of daily self-assessments, in order to determine the following endpoint of the study:

- duration and severity of Covid-19-related symptoms.

In addition, the mental health and well-being of the participants will be monitored by asking them to complete the GAD-7 questionnaire at the screening visit and at the 2- and 4-week visits. The script of the daily telephone interviews includes questions on possible suicidal ideation and impairment of mental health. Should the answers to these questions reveal significant adverse changes from baseline or an elevated risk for self-harm, the investigator will be informed, and will then take the necessary actions to provide appropriate psychiatric evaluation and care for the subject, without delay.

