**Appendix 3: Telephone assessment form**

- 1) Yleisvointi asteikolla 0-10 (0 = huonoin mahdollinen; 10 = täysin terve verrattuna nykyistä sairautta edeltävään tilanteeseen)
- 2) Hengenahdistuksen tunne asteikolla 0-10 (0 = ei hengenahdistusta; 10 = paha hengenahdistus levossakin)
- 3) Pulssioksimetrin lukema soiton aikana mitattuna \_\_\_\_\_ ja aamulla pian heräämisen jälkeen \_\_\_\_\_
- 4) Kuumeen mittaustulos yhden desimaalin tarkkuudella aamulla heräämisen jälkeen \_\_\_\_\_
- 5) Onko muilla samassa taloudessa asuvilla saman sairauden oireita? Kenellä? Milloin ne alkoivat?
- 6) Oletteko tuntenut itsenne sekavaksi, masentuneeksi tai poikkeuksellisen jännittyneeksi viime päivien aikana?
- 7) Lääkkeen mahdolliset haittavaikutukset edellisen kyselyn jälkeen:  
\_\_\_\_\_
- 8) AE ja SAE raportointi tutkimuksesta vastaavalle lääkärille (luettelo mahdollisista haittatapahtumista alkamisaikoihin)
- 9) Muut mahdolliset oireet

Tutkittavan numero tutkimuksessa: \_\_\_\_\_

Puhelinhaastattelun päiväys ja kellonaika. Vastaukset koskevat tätä päivää:

\_\_\_\_\_

pp kk vuosi klo hh.min

Haastattelija (nimikirjoitus ja nimen selvennys):

Tutkimuskeskus(tutkimukseen osallistuva terveyskeskus):

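### Appendix 3, the protocol's only telephone form, has no suicidal-ideation item (0 of 9), although Sections 6.2 and 7.2.2 say the daily telephone script asks about it

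*Protocol*

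**What the plan says.** Section 6.2 describes the daily calls to subjects who have symptoms and states: "The script of the daily telephone interviews includes questions on possible suicidal ideation and impairment of mental health". Section 7.2.2 says the same. Both sections attach an action: should the answers "reveal significant adverse changes from baseline or an elevated risk for self-harm, the investigator will be informed", and the investigator must then arrange psychiatric evaluation and care promptly. Section 3.3 gives the calls a data-collection role as well: "Daily telephone contacts by the study sites are included in the standard care protocol; also, they will be used for collection of patient-reported information".

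Appendix 3, in Finnish, is the only telephone form among the three appendices. Its one mental-health item is item 6: "Oletteko tuntenut itsenne sekavaksi, masentuneeksi tai poikkeuksellisen jännittyneeksi viime päivien aikana". In English, it asks whether the subject has felt confused, depressed or unusually tense in recent days.

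**The concern.** The protocol names two topics for the daily script, suicidal ideation and impairment of mental health. The form in the appendix covers only the second. A caller who works down the form as printed would not be prompted to ask about ideation. The self-harm part of the trigger would then depend on a general mood question or on what the subject volunteers.

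What is at stake is a safeguard the protocol has already committed to. Section 1.3 lists affect lability among the most common side effects of HCQ, so a question aimed at new ideation during illness and treatment has a purpose. No efficacy or safety analysis depends on the answer.

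**Working it through.** No arithmetic beyond a count applies, and the protocol gives no figure to reproduce. The check has two steps.

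**Step 1. Compare the form with the promise.** Items of Appendix 3, translated and shortened:

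| Item | Content | Mental health? | Suicidal ideation or self-harm? |
|---|---|---|---|
| 1 | General condition, 0-10 | no | no |
| 2 | Breathlessness, 0-10 | no | no |
| 3 | Oximeter reading during the call and after waking | no | no |
| 4 | Morning temperature | no | no |
| 5 | Similar symptoms in the household | no | no |
| 6 | Confused, depressed or unusually tense | yes | no |
| 7 | Possible side effects of the drug | no | no |
| 8 | AE and SAE reporting to the responsible physician | no | no |
| 9 | Other symptoms | no | no |

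Mental health: 1 of 9 items. Suicidal ideation or self-harm: 0 of 9 items.

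**Step 2. Ask whether Appendix 3 is the form for the daily calls.** The body text never cites Appendix 3, so this has to be inferred.

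Pointing towards daily use:
- The date line, placed after item 9, reads "Puhelinhaastattelun päiväys ja kellonaika. Vastaukset koskevat tätä päivää": the answers concern that day.
- Item 7 is worded "Lääkkeen mahdolliset haittavaikutukset edellisen kyselyn jälkeen", that is, since the previous query. The form is therefore used more than once per subject.
- Items 3 and 4 ask for oximetry and morning temperature. Section 6.2 provides oximeters for the first 14 days, and the Table 1 footnote on patient-reported outcomes reads "Includes body temperature and pulse oximetry results recorded at home by the patient, until the 2-week visit".

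Leaving it open:
- Item 6 asks about recent days, not the current day.
- The Day 8 call also falls within the oximeter period. The synopsis and Section 3.3 describe it as an interview on symptoms and possible AEs, which the form can hold. Only Section 6.2 adds concomitant medications, for which the form has no item. The form may serve the daily calls and Day 8 alike.
- Section 11.2 says study-specific source data forms are to be prepared before the study starts, so a fuller script may exist outside the protocol.

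The count in Step 1 is certain. The link in Step 2 is a reasonable inference that the protocol does not confirm.

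**The case against.** The strongest reply is that no contradiction is proved. Sections 6.2 and 7.2.2 speak of a script, whereas Appendix 3 is titled as an assessment form and reads largely as a recording sheet; only items 5 and 6 are phrased as questions to the subject. A recording sheet need not print every scripted question. The obligation also stands in the body text, stated twice, and staff are bound by it whatever the form shows. This part of the reply holds, and it limits the point to a form that does not visibly deliver what the text promises.

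The second reply is that other layers cover the risk. Exclusion criterion 9 states: "prior history of suicidal behaviour or suicide attempt within five years of screening will also exclude the subject". Item 6 can lead to follow-up questions, items 7 to 9 leave room for a spontaneous report, and the GAD-7 is completed at screening and at the 2- and 4-week visits. These layers reduce the risk, but none asks about new ideation. The exclusion is applied at screening and looks back, the protocol uses the GAD-7 for anxiety symptoms, and items 7 to 9 do not raise the subject.

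A reader might infer that the trial does not monitor suicidal ideation at all, or that the promised mental-health questioning is missing altogether. The documents support neither. Item 6 meets the mental-health part of the promise, and nothing in the protocol rules out a separate script that contains the ideation question.

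**Conclusion.** The concern holds as a minor internal inconsistency in safety monitoring. Sections 6.2 and 7.2.2 describe a suicidal-ideation question in the daily script, and the only telephone form supplied has none among its nine items. The practical consequence, that the question is not prompted, rests on two assumptions: that Appendix 3 is used for the daily calls, which its content suggests but no text states, and that it is used as printed without a supplementary script. The scope is the daily calls to subjects with symptoms; the protocol promises the question in no other contact, so no shortfall is claimed elsewhere. Endpoints, sample size and analysis are unaffected.

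**What to change.** Add one explicit item on suicidal ideation to Appendix 3, next to item 6, with a printed prompt to notify the investigator if the answer raises concern. Cite Appendix 3 in Sections 6.2 and 7.2.2 so that its role is stated. If a separate script already contains the question, cite that script in both sections instead, and add a field to Appendix 3 to record the answer.

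The cost is a one-page form revision, a cross-reference in two sections and one brief question per call.
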